##### Statistical Analysis

An evaluation of the new intervention will be done through comparison of primary outcomes and secondary outcomes between the intervention group and control group of the trial at baseline and 12-month follow-up. Results will be presented as SAQ-DK mean scale scores and SD, using Poisson regression statistical modeling.

*Qualitative data* will be transcribed and stored according to the current law. A structured codebook will be generated to guide thematical analysis [64]. Analysis will be performed by a junior researcher triangulating findings with a senior researcher with expertise in the qualitative research field, using NVivo (QSR International) [65].

*Quantitative data* will be registered and stored in REDCap [66] subsequently being transferred for analyses in Stata (StataCorp).

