**Methods:**

The fully integrated mixed method study will be conducted using an integrated knowledge translation approach. Patient safety culture within nursing homes will first be explored through qualitative focus groups (stage 1) including nursing home residents, their relatives, and frontline health care providers. This will inform the development of an intervention in a multidisciplinary panel (stage 2) including cocreators representing the medication management process across the health care system. Evaluation of the intervention will be done in a randomized controlled trial set at nursing homes (stage 3). The primary outcome will be changes in the mean scale score of an adapted version of the Danish “Safety Attitudes Questionnaire” (SAQ-DK) for use in nursing homes. Patient safety–related outcomes will be collected through Danish health registers to assess safety issues and effects, including medication, contacts to health care, diagnoses, and mortality. Finally, a mixed methods analysis on patient safety culture in nursing homes will be done (stage 4), integrating qualitative data (stage 1) and quantitative data (stage 3) to comprehensively understand patient safety culture as a key to medication safety.

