##### Study Sample and Size

A total of 36 public nursing homes were registered within the Municipality of Aalborg in 2021. We expect to recruit a minimum of 22 nursing homes to participate in this phase. Inclusion criteria are the following: to be eligible for inclusion within this study, nursing homes must be supported by a general practitioner registered by the Municipality of Aalborg. Exclusion criteria are the following: if a conflict appears, for example, in relation to other initiatives targeting medication, the Municipality will ensure exclusion of specific nursing homes. Nursing home care staff will be included according to the overall eligibility criteria and definitions defined in Table 1.

As no other studies have investigated the effect of a complex intervention in a mixed methods study design in primary care on SAQ, the sample size cannot be based exclusively on previous study outcomes. We aim to recruit as many respondents as possible from the included nursing homes.

Based on previous studies focusing on related health care setting and culture, we expect mean scale scores of SAQ of 32 to 75 [62,63], and we expect to find an increase of at least 4.0. We expect a lower SD than that reported in previous studies, as these studies have investigated more variable groups of professions. The overall SD (all domains) in home care services have been reported as 9.8 [62]. Thus, with a power of 0.8, significance level (α) of .05, and an expected SD of 9.8, it has been estimated that 192 respondents (96 respondents in the intervention group and 96 respondents in the control group) will be sufficient.

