##### Outcomes

The initial problem statement that emerged from the Municipality of Aalborg was that adverse events were increasingly reported, yielding a legally bound challenge that is not yet overcome. Thus, the Municipality sought help for lowering the number of medication errors and unsafe medication practices through collaboration. Although reporting adverse events is an intended goal in safety terms in Denmark, the number of adverse events is not a proper estimate of medication safety.

As a proxy for the overall medication safety, including medication errors, the SAQ has been suggested. A Danish reliable and valid version is available (Danish Safety Attitudes Questionnaire, SAQ-DK). An increase in SAQ-DK would indicate a decrease in medication errors, whereas a decrease would indicate a worsening. We are aware of using the SAQ-DK as the primary outcome with precaution, as the intended increase in reporting adverse events within primary care is still an ongoing issue. However, to the best of our knowledge, no other more suitable measure is available, and therefore, we chose the SAQ as the most reliable and relevant proxy for medication safety in the SAME study.

The primary outcome will be focused on the nursing home frontline, including nursing home care staff’s and nursing home managers’ (Table 1) self-reported perceptions of patient safety culture measured as mean scale SAQ-DK score [36]. The SAQ-DK will be adapted for use in Danish primary health care settings, including nursing homes following the cocreative approach of the SAME study.

Secondary outcomes will include the following: qualitative—perceptions of patient safety culture of relevant cocreators collected through semistructured focus group interviews or individual interviews, depending on the results of the research process; quantitative—register data; that is, sociodemographic data and data on health-related outcomes will be collected at baseline and at follow-up. Data will be collected from relevant Danish registries.

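### The primary outcome is a change in one place and a score in another, and the analysis names no single effect contrast and no use of the baseline; a baseline-adjusted follow-up comparison would settle this and keep at least the planned power

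*Protocol article*

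**What the plan says.** Four statements in the protocol article bear on the primary analysis.

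- Abstract, Methods: "The primary outcome will be changes in the mean scale score of an adapted version" of the Danish questionnaire. The outcome is a change.
- Stage 3, Outcomes: "self-reported perceptions of patient safety culture measured as mean scale SAQ-DK score". The outcome is a score, and change is not mentioned.
- Stage 3, Statistical Analysis: a "comparison of primary outcomes and secondary outcomes between the intervention group and control group of the trial at baseline and 12-month follow-up". The next sentence adds: "Results will be presented as SAQ-DK mean scale scores and SD, using Poisson regression statistical modeling". No contrast of change and no baseline covariate is named.
- Stage 3, Study Sample and Size: "we expect to find an increase of at least 4.0". The SD comes from an earlier study: "The overall SD (all domains) in home care services have been reported as 9.8". The calculation is made "with a power of 0.8, significance level (α) of .05, and an expected SD of 9.8", giving 192 respondents, 96 in each arm. The SD is not described as that of a change, and no correlation between baseline and follow-up is given.

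The Results section reports that baseline SAQ-DK data were collected in January 2022, so a baseline measurement exists.

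**The concern.** A trial needs one number that carries its conclusion. Here it could be the difference between arms at follow-up, the difference between arms in change, or something drawn from two comparisons, one of them at baseline. The baseline comparison cannot show an effect: between randomised arms, before rollout, any difference is chance.

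The choice among the others matters in two ways. First, their precision differs, and the sample size fits only some of them. Second, an unadjusted follow-up comparison leaves in the result whatever part of a chance baseline imbalance persists, although the data to remove it are in hand. If the choice is left open until follow-up scores are seen, different analyses could give different answers and the text would support more than one of them.

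**Working it through.** **Inputs.** From Study Sample and Size: difference 4.0, SD 9.8, α 0.05, power 0.80, 96 per arm. Assumed, because the article does not give them: a two-sided test, equal SDs at both surveys, and r, the correlation between a respondent's baseline and follow-up scores. I show r = 0, 0.3, 0.5 and 0.7.

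**Step 1: reproduce the plan's figure.** A two-sided two-sample t-test with standardised difference 4.0/9.8 = 0.408 needs 95.2 per arm, rounded up to 96, or 192 in total. This matches the article. Power at 96 per arm is 80.3%. A one-sided test would need about 75 per arm and does not match. The calculation is therefore that of an unadjusted comparison of one score between two independent groups.

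**Step 2: power of the candidate analyses at 96 per arm.**

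- Follow-up score, unadjusted: SD = 9.8
- Change score: SD = 9.8 × √(2(1 − r))
- Follow-up score adjusted for baseline: SD = 9.8 × √(1 − r²)
- SE of the between-arm difference = SD × √(2/96)

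| r (assumed) | Change: SD | SE | Power | Adjusted: SD | SE | Power |
|---|---|---|---|---|---|---|
| 0 | 13.86 | 2.00 | 51% | 9.80 | 1.41 | 80% |
| 0.3 | 11.60 | 1.67 | 66% | 9.35 | 1.35 | 84% |
| 0.5 | 9.80 | 1.41 | 80% | 8.49 | 1.22 | 90% |
| 0.7 | 7.59 | 1.10 | 95% | 7.00 | 1.01 | 98% |

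The unadjusted follow-up comparison has SE 1.41 and power 80% at every r. The change score falls below the plan when r is under 0.5 and exceeds it when r is above 0.5. The adjusted comparison is never below the plan. The individual-level figures need the same respondents, linked, at both surveys. If the respondents differ, no personal change score exists, and the r = 0 row then describes a difference in differences between independent samples.

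**Step 3: chance imbalance.** Ignoring clustering, the SE of the baseline difference is also 1.41. An imbalance of 2 points or more in either direction, half the target effect, then has probability of about 16% (z = 2/1.41). The expected carry-over into an unadjusted follow-up difference is r times the imbalance: 1 point at r = 0.5.

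**Step 4: clustering.** The unit of randomisation is not stated. If it is the home, 192/22 = 8.7 respondents per home gives a design effect of 1 + 7.7 × ICC. For assumed ICCs of 0.01, 0.05 and 0.10 this is 1.08, 1.39 and 1.77, and the unadjusted power falls to about 78%, 67% and 57%. The Step 2 figures are thus upper values, useful for comparing the analyses with each other.

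**The case against.** Several points on the other side are sound.

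*A reader might infer that the arms will be tested separately at each time point.* The text does not say so. The sentence also fits one contrast that uses both surveys, which the abstract's change outcome and the expected increase would suggest. What stands is that no contrast is named.

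*A reader might infer that the trial is underpowered because it was sized with the SD of a single score.* Step 1 shows otherwise: for an unadjusted follow-up comparison that SD is the right one. The shortfall arises only if change scores are analysed and r is below about 0.5. At r = 0.7 a change-score analysis would have 95% power.

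*Covariates are normally left to the statistical analysis plan.* This is true, and a condensed article's silence on adjustment would not be a finding by itself. The finding rests on what is written: two definitions of the primary outcome, and a comparison statement that includes baseline and singles out no effect. Adjustment is proposed as the best way to resolve that.

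*The gain is conditional.* This also stands. It needs linked respondents, r above zero and a linear model, whereas the article names Poisson regression. It does not deal with clustering.

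**Conclusion.** The point holds as an inconsistency of definition with an inexpensive remedy. The primary outcome is worded as a change and as a score, and the Statistical Analysis section neither picks a single effect contrast nor uses the baseline. The sample size is correct for an unadjusted follow-up comparison at about 80% power. Under a change-score analysis, power could lie anywhere from about 51% (r = 0) to 95% (r = 0.7). Baseline adjustment gives about 80% to 98% over the same range, so among the three it is the one that is safe whatever r proves to be.

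These figures assume linked respondents, equal SDs at both surveys, a linear model and no clustering. The documents support neither a claim that the stated sample size is wrong nor a claim that adjustment alone secures 80% power if homes were randomised.

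**What to change.** Use one definition in the abstract, in Outcomes and in Statistical Analysis: the primary estimate is the between-arm difference in follow-up SAQ-DK mean score, with its confidence interval, from a linear model adjusted for the baseline score. State whether responses are linked across the two surveys, and choose the covariate accordingly:

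- if they are linked, each respondent's own baseline score;
- if they are not, the home's baseline mean for every respondent.

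Do not mix the two in one covariate. They are different quantities with different slopes and measurement error, so a single coefficient would have no clear meaning. Present baseline values by arm descriptively, without a between-arm test. Settle this before follow-up scores are examined by arm.

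The cost is small: one covariate already collected, some rewording, and a linear model in place of the named Poisson model for this outcome. Without linkage the gain is smaller and comes only through differences between homes. If homes are the randomised unit, the model must also allow for clustering, which baseline adjustment does not replace.

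### Poisson regression is named for the SAQ-DK mean scale score, an averaged score sized as a difference in means; its model-based standard errors are not valid for this outcome

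*Protocol article*

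**What the plan says.** The Outcomes section of the protocol article defines the primary outcome as "self-reported perceptions of patient safety culture measured as mean scale SAQ-DK score", so it is an average over questionnaire items and not a number of events.

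Study Sample and Size treats it as a continuous score. It states "we expect mean scale scores of SAQ of 32 to 75" and "we expect to find an increase of at least 4.0". It takes its spread from one earlier study: "The overall SD (all domains) in home care services have been reported as 9.8". The calculation is made "with a power of 0.8, significance level (α) of .05, and an expected SD of 9.8" and concludes that "192 respondents (96 respondents in the intervention group and 96 respondents in the control group) will be sufficient". The same paragraph says that the authors expect less spread than earlier studies found, but it gives no other value and uses 9.8.

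Statistical Analysis then names the model: "Results will be presented as SAQ-DK mean scale scores and SD, using Poisson regression statistical modeling". It mentions no robust variance, dispersion parameter or alternative model. The register outcomes, some of which are counts, are covered under Safety Assessments and Effects, where the groups are to be compared descriptively.

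**The concern.** The model named for the primary outcome does not match the outcome or the sample size calculation. Poisson regression is a model for counts. Its standard errors come from the assumption that the variance equals the mean, and nothing about an averaged attitude score makes that true. If the variance is larger than the mean, the standard errors are too small and the test rejects too often. If it is smaller, the test is too cautious and loses power. In its usual log-link form the model also reports a ratio of means, whereas the trial is planned around a difference in points.

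At stake are the error rate of the trial's main test and the scale on which its main result is reported.

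**Working it through.** **Inputs.** From Study Sample and Size: difference 4.0, SD 9.8, expected means 32 to 75, alpha .05, power 0.8, 96 per group. From Statistical Analysis: Poisson regression, with no variance estimator stated.

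**1. Reproduce the plan's sample size.** The normal approximation for two means, two-sided, is n per group = 2 × (1.96 + 0.84)² × SD² / difference². This gives 2 × 7.85 × 96.04 / 16 = 94.2, rounded up to 95. The t-test version gives 95.2, rounded up to 96 per group and 192 in total, which is the stated figure. A one-sided test gives 75 per group and does not reproduce it. The trial is therefore sized as a two-sided comparison of two means.

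**2. Compare the variance with what Poisson assumes.** The variance is 9.8² = 96.04. Poisson takes it to equal the mean, so:
- dispersion = 96.04 / mean
- model-based SE / true SE = √mean / 9.8
- true size of a nominal 5% test = 2 × (1 − Φ(1.96 × √mean / 9.8))

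| Mean | Dispersion | Model SE / true SE | True size |
|---|---|---|---|
| 32 | 3.00 | 0.577 | 25.8% |
| 50 | 1.92 | 0.722 | 15.7% |
| 75 | 1.28 | 0.884 | 8.3% |

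**3. Check by simulation.** There were 4,000 trials with no effect at each mean, with 96 independent respondents per arm and normal scores with SD 9.8, clipped to 0–100 (an assumed scale).

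| Analysis | Rejections at mean 32 | Rejections at mean 75 |
|---|---|---|
| Poisson, model-based SE | 25.2% | 8.9% |
| Poisson, robust SE | 4.7% | 5.6% |
| Linear model | 4.6% | 5.4% |

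**4. Vary the residual SD.** The same formula is used, with the residual SD in place of 9.8.

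| Residual SD | True size at mean 32 | True size at mean 75 |
|---|---|---|
| 9.8 | 25.8% | 8.3% |
| 8.66 | 20.0% | 5.0% |
| 8 | 16.6% | 3.4% |
| 7 | 11.3% | 1.5% |
| 5.66 | 5.0% | 0.3% |

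The break-even SD is √mean: √75 = 8.66 and √32 = 5.66. Adjusting for baseline reduces the residual SD to 9.8 × √(1 − r²). With an assumed correlation r of 0.5 this is 8.49, and the size is 19.1% at mean 32 and 4.6% at mean 75. With r = 0.7 it is 7.00, and the size is 11.3% and 1.5%.

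**5. Scale of the effect.** A rise of 4.0 points is a ratio of 36/32 = 1.125 from a mean of 32, but 79/75 = 1.053 from a mean of 75. The default Poisson output therefore gives the planned effect no single value.

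**The case against.** There are four serious points on the other side.

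- **The article is silent on the variance estimator.** A condensed article may leave that detail to a fuller document, and step 3 shows that robust standard errors bring the test back to about 5%. This stands as a condition on the error rates. It does not remove the point, because the choice of model is stated and does not suit the outcome.

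- **The quoted rates need SD 9.8 and an unadjusted comparison.** The plan itself expects less spread. This stands. The pairing of mean 32 with SD 9.8 is also not made in the text: the range of means is cited to two sources and the SD to only one of them. The 26% is thus the edge of the plan's stated range and not a forecast.

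- **A reader might infer that the Poisson model cannot estimate the 4.0-point difference.** The documents do not support that. A two-arm Poisson fit reproduces the arm means exactly, so the difference in points can be recovered, and the article already plans to present means and SDs. What remains is that the default effect measure is a ratio, while the trial is sized in points.

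- **A reader might think the Poisson sentence was meant for the register counts.** The sentence names SAQ-DK, and Safety Assessments and Effects plans only descriptive comparison for the register outcomes.

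**Conclusion.** The point holds in conditional form. The article names a count model for an averaged score whose sample size rests on comparing two means, and this mismatch does not depend on any assumption about the SD.

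The size of the error does depend on assumptions. With model-based standard errors, no adjustment, independent respondents and the plan's SD of 9.8, the true type I error runs from about 26% at mean 32 to about 8% at mean 75. A reader might infer that the trial will have 8% to 26% false positives whatever is done. That is too strong, because both the size and the direction of the error change with the residual SD and with the choice of standard error. The unpredictability is itself the defect: the validity of the test would rest on an accidental match between variance and mean.

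Correlation among respondents from the same nursing home is a separate matter and is not part of these figures.

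**What to change.** In Statistical Analysis, replace Poisson regression for SAQ-DK with a linear model for the difference in mean score between arms. The model should:
- allow for nursing home, by a random intercept or cluster-robust standard errors;
- adjust for baseline score, using the individual score if respondents can be linked between the two surveys and the home-level baseline mean if not;
- report the difference in points with a 95% confidence interval.

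If Poisson is kept, state cluster-robust standard errors and report the effect as a difference in points.

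This point calls for no change to the register outcomes, for which descriptive statistics are planned.

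The cost is about one sentence of text. Stata, already named, fits either model, and baseline scores are already collected. The one thing to settle first is whether individual respondents can be linked across the surveys, which the article does not say. The home-level baseline mean avoids that dependence.

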##### Safety Assessments and Effects

Patient safety–related outcomes will be analyzed through quantitative data collected through national registers; these data include (1) medication (number and type); (2) contacts to a health care system (hospital, nursing home general practitioner, and out-of-hour general practitioner); (3) diagnoses (somatic and psychiatric 10th revision of the International Statistical Classification of Diseases diagnoses); and (4) mortality. Descriptive statistics will be used to compare groups.

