### Study Objective and Research Questions

Therefore, the primary objective of the Safe Medication in Nursing Home Residents (SAME) study is to develop and evaluate an intervention to improve medication safety of nursing home residents through patient safety culture. First, we aim to develop an intervention to improve medication safety of nursing home residents in a cocreative process, including (1) exploration of patient safety culture as perceived at the frontline of nursing homes (stage 1) and (2) development of a knowledge-based intervention in a multidisciplinary panel informed by findings from focus groups interviews exploring patient safety culture (stage 2). Second, we aim to evaluate the intervention in a randomized controlled trial (RCT) set at nursing homes (stage 3), including a register-based study on patient safety–related outcomes in nursing home residents. Finally, we aim to perform an integrative mixed methods analysis on patient safety culture in nursing homes to comprehensively understand patient safety culture as a complex phenomenon and target of medication safety improvement (stage 4). This could potentially drive a new theory on patient safety culture to guide future efforts to improve medication safety of older adults living in nursing homes. Using an integrated knowledge translation (IKT) approach, we aim to enhance knowledge translation from research into practice through generation of partnership-based, meaningful, acceptable, and feasible results to address medication safety in nursing homes, incorporating the voices of nursing home residents and their relatives. As no current golden standard exists for IKT approach in research, and as the existing guiding tool is based on general assumptions toward cocreativity and knowledge creation, we chose to pragmatically use the 8 guiding principles of IKT [48] that was recently developed to guide research on spinal cord injury, but follow general assumptions and definitions concerning cocreation and knowledge generation, to frame the overall research process of the SAME study. In addition, the IKT project proposal worksheet [49] based on the Canadian Institutes of Health Research’s merit review criteria [50] will be used in the secondary objectives, which are to (1) explore and identify patient safety culture perceived by knowledge users at the frontline of nursing homes, including health care providers and receivers, and find out whether it is possible to explicitly describe implicit, core elements of patient safety culture through in-depth qualitative explorative analysis; (2) cocreate an intervention within existing resource frame to increase medication safety in nursing homes by including stakeholders and knowledge users, and it is based on patient safety culture as perceived at the frontline and guided by Safety II theory; (3) explore the impact of cocreativity in the development of an acceptable and feasible complex intervention to improve medication safety through patient safety culture in nursing homes; (4) develop new, comprehensive understanding of patient safety culture as a complex target to improve medication safety within high-risk complex primary care settings through mixed methods integrative analysis including both in-depth qualitative data on patient safety culture and quantitative data on patient safety climate in nursing homes; and (5) describe the impact of the intervention on quantitative health-related outcomes for safety assessment.

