### Work Package 2: Evaluation of Intervention and Understanding of Patient Safety Culture

#### Stage 3: Quantitative Evaluation of the New Intervention in an RCT

In stage 3, we will evaluate the new intervention in a randomized controlled study set at nursing homes. Data on primary outcome will be collected at baseline before rollout of the intervention and at 6-month to 9-month follow-up according to intervention rollout at individual participating nursing homes. Data on secondary outcomes will be collected during the intervention period.

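### Resident register outcomes, including mortality, are to be compared between arms by descriptive statistics only, and the article gives no single counting window for them

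*Protocol article*

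**What the plan says.** The Safety Assessments and Effects section introduces the resident data with "Patient safety–related outcomes will be analyzed through quantitative data collected through national registers". It lists medication, contacts with hospital and general practice, diagnoses and mortality, and ends with "Descriptive statistics will be used to compare groups".

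Two other places give these outcomes their purpose. The abstract's Methods paragraph collects them "to assess safety issues and effects, including medication, contacts to health care, diagnoses, and mortality". The fifth secondary objective, in Study Objective and Research Questions, is to "describe the impact of the intervention on quantitative health-related outcomes for safety assessment".

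Three places in the article bear on timing:

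- The opening of Stage 3: "Data on secondary outcomes will be collected during the intervention period". The same paragraph puts primary-outcome follow-up at 6 to 9 months, depending on rollout in each home.
- Stage 3, Outcomes: "sociodemographic data and data on health-related outcomes will be collected at baseline and at follow-up".
- Statistical Analysis: "comparison of primary outcomes and secondary outcomes between the intervention group and control group of the trial at baseline and 12-month follow-up". The only regression model named there, Poisson, is attached to the SAQ-DK scores.

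The Results section adds a calendar: SAQ-DK baseline in January 2022 and follow-up expected in January 2023.

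**The concern.** An effect or impact in a randomized trial is a contrast between arms, and a reader can weigh it only together with its uncertainty. Here the article makes a positive choice of method, and that choice carries no stated uncertainty. It matters more than usual because the primary outcome is a staff-reported proxy, which the article itself says it uses with caution. The register data are the trial's only quantitative health outcomes for residents.

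Residents live in homes and the intervention is rolled out by home, so outcomes within a home may be correlated. Bare percentages show neither the sampling error nor that correlation. The risk is that two similar percentages are taken as reassurance when the data could not have shown otherwise.

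The window matters because deaths and contacts are counts over time. If the length of observation follows each home's rollout, unequal exposure could create a difference or hide one.

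**Working it through.** **1. The plan's only sample-size figure.** Study Sample and Size in Stage 3 gives 192 staff respondents (96 per group) for a 4.0-point SAQ difference, SD 9.8, power 0.80 and alpha 0.05.

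- Normal approximation: n per group = 2 × (1.960 + 0.842)² × 9.8² / 4.0² = 94.2, so 95 per group and 190 in total.
- The t-distribution version gives 96 per group, 192 in total.

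The figure reproduces, but it concerns staff scores. It says nothing about precision for residents. The article gives no resident numbers, event rates or harm margin.

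**2. Precision for resident mortality (illustration).**

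From the document: at least 22 homes.

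Assumed, because the article does not give them:

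- homes as the units allocated, split 11 and 11
- m = 30 to 60 residents per home
- 12-month mortality p = 20 to 30%
- ICC = 0 to 0.05

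Formulas:

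- Design effect: DE = 1 + (m − 1) × ICC
- Effective residents per arm: n_eff = 11m / DE
- SE of the risk difference: √(2p(1 − p) / n_eff)
- 95% half-width: t(0.975, 20 df) × SE = 2.086 × SE

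| m | p | ICC | DE | n_eff | Half-width (points) |
|---|---|---|---|---|---|
| 60 | 20% | 0 | 1.00 | 660 | 4.6 |
| 45 | 20% | 0.01 | 1.44 | 344 | 6.4 |
| 45 | 30% | 0.01 | 1.44 | 344 | 7.3 |
| 30 | 20% | 0.05 | 2.45 | 135 | 10.2 |
| 30 | 30% | 0.05 | 2.45 | 135 | 11.6 |

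For the last row: √(2 × 0.30 × 0.70 / 134.7) = 0.0558, and 2.086 × 0.0558 = 0.116.

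The first and last rows are the extremes of the grid. Identical observed mortality in the two arms would be compatible with a true excess of roughly 5 to 12 points. Over the same grid, the risk ratio detectable with 80% power runs from about 1.24 to 1.76.

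**3. Effect of the window.** With a constant hazard, the proportion dead by month k is 1 − (1 − p)^(k/12).

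| Assumed 12-month mortality | 6 months | 9 months | 12 months |
|---|---|---|---|
| 20% | 10.6% | 15.4% | 20% |
| 30% | 16.3% | 23.5% | 30% |

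Going from 6 to 12 months nearly doubles the deaths counted. At the same hazard, two homes observed for 6 and 9 months would differ by 15.4 − 10.6 = 4.8 points (20% case) or 23.5 − 16.3 = 7.2 points (30% case) from window length alone. These differences are of the same order as the half-widths above.

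**The case against.** Descriptive safety reporting is common, and the fifth secondary objective says describe. The safety sentence does not rule out differences or intervals, and Statistical Analysis separately promises a between-group comparison of secondary outcomes. The full protocol and analysis plan are not shown, and estimators and cohort definitions are often left to them.

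Part of this stands. The article sets no test or margin and claims no proof of safety, and an unseen plan may say more. But the article does not leave the method open. It names one for exactly these outcomes, and the only model it names belongs to the SAQ-DK. An estimate with an interval remains descriptive reporting, so asking for one does not change the aim.

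On timing, the statements can partly be reconciled. Collecting register data at baseline and follow-up may simply mean the dates of extraction, and an extraction at follow-up can cover everything since baseline. The intervention-period sentence also covers the qualitative secondary outcomes, so it is not a specific rule for counting resident events.

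That disposes of a stronger reading. A reader might infer a two-point snapshot that sees only survivors and new admissions and so misses the deaths and contacts in between. The documents do not state such a design. Mortality and contacts are on the outcome list, and a survivor-only snapshot could not measure mortality, so the extraction reading fits better. What remains is that neither reading says when counting stops: 6 to 9 months by home, 12 months, or the end of the intervention period.

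**Conclusion.** The concern holds in a limited form. For outcomes meant to assess safety and effects, the article states a comparison with no measure of uncertainty and gives no single window over which to count events. On the assumed inputs above, the unreported uncertainty in the mortality difference is about ±5 to ±12 percentage points. Resident numbers, mortality, ICC and the equal split of homes are all assumptions; only the minimum of 22 homes comes from the document.

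A reader might go further and conclude that, because the comparison is descriptive, harm can be neither shown nor ruled out. The documents do not support that. A large imbalance would still be visible in a table. The limit on excluding moderate harm comes mainly from the number of homes and residents, and would remain with intervals. The narrower conclusion is that, as written, the reader cannot judge what the resident data exclude.

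**What to change.** - **Cohort:** define it as residents living in each home at allocation, analysed by allocated arm.
- **Window:** follow them in the registers over one stated window, the same in both arms and in every home.
- **Estimates:** report rate ratios with a person-time offset for contacts, and a risk difference or hazard ratio for mortality. Give each a 95% confidence interval that allows for clustering by home. No hypothesis test is needed. Medication and diagnoses should be summarised on the same cohort and window.
- **Text:** reconcile the opening of Stage 3, its Outcomes section and Statistical Analysis to that window. Say whether baseline and follow-up are extraction dates or observation points.
- **Reporting:** state that similar percentages are not evidence of safety unless the interval supports it.

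The cost is a little more analysis of register data already planned, with no new data collection. With about 22 homes the intervals may still be too wide to exclude moderate harm, but readers will be able to see that.
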